#### Mediation Analyses

In addition, we plan to explore the mediating effects of health behavior constructs such as self-efficacy for taking ART and using health services and perceived social support from health providers, PLHIV, and partners. In mediation analyses, we will estimate both the impact of the intervention on these factors as well as associations between these factors and the post intervention outcomes to partition any observed impacts of treatment into direct and indirect effects. The analytic approach will be based on path analyses using regression analyses or structural equation modeling.

#### Qualitative Analyses

A qualitative data software program, such as QSR Nvivo or QDA Miner, will be used to organize, code, and analyze all qualitative data. Inter-rater reliability checks will be conducted periodically during data coding and analysis, and quantitative coefficients such as Scott’s Pi or Cohen’s Kappa may be used to assess the extent of agreement between coders. Coded data will be analyzed for themes according to the study objectives and research questions. Data will be compared across women, men, and key populations (MSM and FSW) to identify similarities and differences in their reactions to and opinions about the mHealth intervention. Data from facility staff will be analyzed separately from intervention participant data.

#### Cost Effectiveness Analysis

To determine the incremental cost-effectiveness ratio (ICER) of LifeLine, we will relate incremental costs (the numerator) to health effects (the denominator). Specifically, the numerator for the ICER will be calculated as the additional costs associated with implementing the LifeLine program beyond the standard of care. The denominator for the ICER will be calculated from the change in proportion virally suppressed at 12-month follow-up in the LifeLine intervention group compared to the change in proportion virally suppressed in the standard of care group.

Sensitivity analyses will be conducted to model cost-effectiveness under different parameters, such as lower text message costs that may be negotiated with mobile network operators. A tornado diagram will be generated to visually represent the resulting sensitivity analyses to show the costs and savings associated with different scenarios. In addition, the World Health Organization (WHO) threshold for cost-effectiveness [34] of an ICER lower than three times gross domestic product per person will be considered in presenting results from cost-effectiveness analyses. Affordability also will be considered in evaluating cost effectiveness of the intervention; for example, intervention costs and the ICER will be compared to country expenditures on health.

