**Methods:**

The 36-month study will use a facility cluster randomized controlled design (intervention vs standard of care) for evaluating the impact of mHealth on HIV care and treatment. Specifically, we will look at ART adherence, HIV viral load, retention in care, and condom use at 6 and 12-month follow-up. In addition, participant adoption and satisfaction with the program will be measured. This robust methodology will be complemented by qualitative interviews to obtain feedback on the motivational qualities of the program and benefits and challenges of delivery, especially for key populations. Cost-effectiveness will be assessed using incremental cost-effectiveness ratios, with health effects expressed in terms of viral load suppression and costs of resources used for the intervention.

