## Introduction

### Background

Adherence to prevention, care, and treatment recommendations among people living with HIV (PLHIV) is a critical challenge facing HIV service delivery programs. Myriad personal, social, and systems level barriers influence adherence among PLHIV on antiretroviral therapy (ART). Difficulty managing treatment and forgetting to take medications or attend clinic appointments are common reasons for poor adherence [1-4]. Lack of social support, negative perceptions, poor communication with providers, and stigma and discrimination also may limit adherence [2,3]. In resource-poor settings, adherence challenges are amplified by structural and economic constraints such as residential dispersion that requires long travel times and has costs associated with travel and wage loss [3,4]. Key populations are disproportionately less likely to access and remain in care and treatment compared to the general population of PLHIV [5]. Good clinical outcomes depend on high adherence; consistent adherence to ART regimens is associated with reduced HIV RNA (viral load) levels, decreased transmission, higher CD4 cell counts, lower health care costs, and overall improved quality of life [6-9].

Mobile phones offer a promising means to improve patient adherence and health outcomes because they are private, portable, increasingly affordable, and nearly ubiquitous (88% use in Ghana [10]). Mobile phone interventions provide a means to address several of the key barriers to good adherence by providing reminders for care and a direct connection to health providers and facilities [11,12]. Research conducted in East Africa has shown that texting (short message service, SMS) reminders to ART clients’ mobile phones improved adherence and health [13-15]. Due to favorable findings from mobile phones for health (mHealth) interventions, limited proven adherence and treatment support interventions [3,16,17], and the need for a combination of interventions to address the complexities of adherence, mHealth programs are rapidly being scaled up globally [18,19].

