### Justification for Study

Implementation research is needed to keep pace with mHealth program scale-up to provide guidance for optimal delivery and effectiveness of mHealth programs [3,18,20-22]. Although mobile phone reminders have been shown to improve medication adherence among new ART clients in a few health facilities, a trial conducted in one health facility in Cameroon with continuing ART clients did not improve adherence [21]. We have limited information about mHealth program effects on continuing ART clients and subpopulations in large-scale, public-sector HIV care and treatment programs where the majority of PLHIV in Ghana seek HIV care. Since women and key populations eg, female sex workers (FSW), and men who have sex with men (MSM), continue to be disproportionally affected by HIV, it is critical to assess effectiveness among these groups [3,5]. Moreover, the need for adherence support may be greater among continuing ART clients as opposed to new ART clients, as adherence challenges grow over time [23,24]. The support provided by mHealth interventions may influence ART clients’ adherence as well as retention in HIV care and treatment and adherence to other prevention and care directives such as use of condoms. Furthermore, there is little evidence about the motivational behavior change processes through which mHealth interventions improve patient health [25]. It is imperative to understand when, why, and how interventions work to develop a sound understanding of effectiveness to inform program scale-up [25,26]. Lastly, decision-makers and program implementers need mHealth cost-effectiveness data to guide resource allocation [14,27,28].

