**Costing Measures**						
	Costs of routine care	Training; additional staff time; travel for counselors; other	Intervention tracking tool; costing forms	X	X	X
	Costs of intervention	Initial software and hardware/server costs; maintenance for software and server; maintenance for tech support; monthly reporting; SMS costs; message development	Intervention tracking tool; costing forms	X	X	X

^a^Measures administered in intervention facilities only.

^b^Provider interviews will take place approximately nine months after intervention initiation in intervention facilities only.

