#### Costing Measures

Costs will be assessed for implementing the standard of care in NACP/GHS facilities, as well as costs for implementing the LifeLine mHealth intervention. Information from NACP/GHS facility and SHARPER program records will be extracted to account for retrospective and prospective costs, detailed using an Intervention Tracking Tool (ITT) and accompanying prospective costing forms.

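### The ICER numerator is fixed as the added cost of implementing LifeLine, so any difference between arms in routine-care cost is left out, although routine-care costs are to be collected

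*Protocol article*

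**What the plan says.** The Cost Effectiveness Analysis section first says that incremental costs will be related to health effects, then narrows the cost side: "the numerator for the ICER will be calculated as the additional costs associated with implementing the LifeLine program beyond the standard of care". The Methods paragraph of the abstract has the same scope: cost-effectiveness will be assessed "with health effects expressed in terms of viral load suppression and costs of resources used for the intervention". For the effect side: "The denominator for the ICER will be calculated from the change in proportion virally suppressed at 12-month follow-up in the LifeLine intervention group", compared with the same change under standard of care.

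The cost data to be collected are wider than the numerator. The Costing Measures text states: "Costs will be assessed for implementing the standard of care in NACP/GHS facilities, as well as costs for implementing the LifeLine mHealth intervention". Table 1 has two cost rows, each marked at baseline, 6 and 12 months:

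- Intervention: "Initial software and hardware/server costs; maintenance for software and server; maintenance for tech support; monthly reporting; SMS costs; message development".
- Routine care: "Training; additional staff time; travel for counselors; other".

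The Justification for Study says the support may influence clients' "adherence as well as retention in HIV care and treatment and adherence to other prevention and care directives". The Background associates consistent adherence with "higher CD4 cell counts, lower health care costs, and overall improved quality of life". Table 1 makes pharmacy refills an adherence indicator and retention in care an outcome.

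**The concern.** If LifeLine keeps more people on treatment, intervention facilities will dispense more ART and provide more visits and tests. If better adherence prevents illness, they will provide less care of other kinds. Either way, the gain in suppression enters the denominator, while the care resources used or saved along with it do not enter the numerator.

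This matters because of how the result will be read. The article plans to judge the ICER against a WHO threshold of three times GDP per head and against national health spending. Those are health-system yardsticks, and a programme-only cost is not on the same footing. Cost-effectiveness is one of the three study objectives, and the article justifies it by decision-makers' need for data on allocating resources.

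**Working it through.** The article states no cost or ICER figure, so there is nothing to reproduce. The check is of the definition, followed by an illustration.

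**1. Does the stated rule admit a care-cost difference?** The opening reference to incremental costs could. The sentence that defines the numerator ties it to implementing LifeLine, and the abstract limits costs to resources used for the intervention. The intervention row of Table 1 lists technology, messages, reporting and message development. The routine-care row is collected, but the analysis section does not bring a between-arm difference in it into the numerator. ART, visits and laboratory tests are not named in that row, although an open category exists.

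**2. Effect on the ratio.** Let C be total programme cost per participant, D the difference between arms in care cost per participant (intervention minus control), and E the difference in change in proportion suppressed.

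- Programme-only ICER = C / E
- Total-cost ICER = (C + D) / E
- Ratio of the two = 1 + D / C

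E cancels, so the distortion does not depend on how well LifeLine works on suppression. The ratio is 1 only when D = 0.

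**3. Illustration.** All inputs here are assumptions, in arbitrary currency units: C = 10, E = 0.10, care cost 200 per retained patient-year, and each point of retention counted as a full extra year of care.

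| Retention gain | D | Programme-only ICER | Total-cost ICER | Ratio |
|---|---|---|---|---|
| 0 points | 0 | 10/0.10 = 100 | 10/0.10 = 100 | 1.0 |
| 2 points | 0.02 × 200 = 4 | 100 | 14/0.10 = 140 | 1.4 |
| 5 points | 0.05 × 200 = 10 | 100 | 20/0.10 = 200 | 2.0 |
| 10 points | 0.10 × 200 = 20 | 100 | 30/0.10 = 300 | 3.0 |

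**4. Range.** With care cost between 100 and 400 and gains of 0 to 10 points, C = 10 gives ratios from 1.0 to 1 + (0.10 × 400)/10 = 5.0. Letting C vary from 5 to 20 widens this to 1.0 to 1 + 40/5 = 9.0. If each extra retained patient adds only half a year of care, D halves and the two upper ends become 1 + 20/10 = 3.0 and 1 + 20/5 = 5.0. The top of the range is extreme: the Sample Size section assumes about 20% study attrition, so if retention tracked it, a 10-point gain would halve the loss.

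**5. Other direction.** A net care saving of 5 per participant with C = 10 gives 1 − 5/10 = 0.5. Savings above 10 make the numerator negative. The programme-only ICER would show none of this.

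**The case against.** The strongest reply is that this is a choice of perspective. Programme cost per outcome is a legitimate implementer's view, the abstract is open about that scope, and the objective concerns the cost-effectiveness of the intervention. A condensed article may also leave perspective, resource categories and unit costs to the full protocol. In addition, routine-care costing is planned, and the tornado diagram is to show what different scenarios would cost or save; cheaper text messages are only an example of a parameter.

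Much of this stands. Missing unit costs are not a fault, and the study does not ignore care costs. But the numerator is defined here, not left open, and the definition matches neither the data to be collected nor the yardsticks to be applied. Planned collection does not repair a definition that makes no use of it.

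Four stronger readings are tempting and not supported:

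- **That the trial expects higher retention and use of care.** The article says only that the intervention may influence retention. Use of care is not a listed outcome.
- **That the ICER is biased in LifeLine's favour.** Added retention raises cost and avoided illness lowers it. The net direction is unknown.
- **That the omitted cost is several times the cost of the intervention.** No unit costs are given. Setting it against message cost alone would exaggerate, because programme cost also includes software, server, maintenance, support, reporting and message development.
- **That LifeLine staff time will be booked as standard care.** Table 1 puts training and additional staff time under routine care, without saying additional to what. The service is fully automated and study staff supply the phone numbers, so such effort may be small. The placement needs clarifying; it does not show a loss of cost.

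**Conclusion.** The point holds as a mismatch between the ICER definition and the rest of the plan. Followed literally, the numerator is an incomplete increment whenever care costs differ between arms. The size is unknown. The relation 1 + D/C is exact, but the range of 1.0 to 9.0 rests wholly on assumed programme costs, care costs and retention gains, and the true ratio could lie below 1 if care is saved. The point concerns the third objective only; it does not touch the comparison of adherence, suppression or other health outcomes.

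**What to change.** Define the numerator as the difference between arms in total health-system cost per participant over 12 months: LifeLine programme cost plus routine-care cost. Routine-care cost should cover ART dispensed, visits, laboratory tests and, where facility records hold it, care for illness. Adding only ART and visits would count the extra costs and miss the possible savings.

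Report the programme-only ICER alongside, labelled as the implementer's perspective. Make the care-cost term one of the parameters varied in the planned tornado diagram. In Table 1, place any training or staff time caused by LifeLine under intervention costs.

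The cost is modest. Pharmacy, clinical and costing records are already planned, and the study ended before ethics approval and is seeking new funding, so the text can still be changed. The work is wording, an adjustment to the costing form, and applying unit costs to the records. The price is a noisier and possibly less favourable ICER.

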### Analysis

#### Primary Analyses

Generalized estimating equations (GEE) will be applied to compare intervention and control arms on the key 6 and 12-month health outcomes. In order to adjust for variance in the outcomes at the facility-level, compound symmetric working correlation matrices will be used in all models. In order to maximize statistical power, all models will control for baseline measures of the outcomes. In addition, all models will include sex, stratification variables, and time on ART, as well as other covariates identified from the literature and to be specified in the final statistical analysis plan. Hypotheses will be tested at the 5% significance level for two-sided comparisons.

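### The ICER denominator is specified as a difference in changes in viral suppression and is not tied to the baseline-adjusted, cluster-aware model planned for the same outcome

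*Protocol article*

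**What the plan says.** The Cost Effectiveness Analysis section of the protocol article defines the health effect in the ICER in one sentence: "The denominator for the ICER will be calculated from the change in proportion virally suppressed at 12-month follow-up in the LifeLine intervention group". The comparator is the matching change in the control arm. Table 1 lists viral suppression (below 400 copies/ml) at baseline and month 12, so the change is from baseline to month 12. The section does not refer to the models described under Primary Analyses. On uncertainty it says: "Sensitivity analyses will be conducted to model cost-effectiveness under different parameters, such as lower text message costs", and then "A tornado diagram will be generated to visually represent the resulting sensitivity analyses".

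Viral suppression is also one of the health outcomes that Primary Analyses compares between arms by GEE. There, "In order to maximize statistical power, all models will control for baseline measures of the outcomes". The same paragraph lists further covariates ("all models will include sex, stratification variables, and time on ART") and, to deal with facility-level variation, states that "compound symmetric working correlation matrices will be used in all models".

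**The concern.** The protocol adjusts for baseline in its health-outcome models expressly to gain power. It then writes the ICER denominator in a form that gives up part of that gain. Subtracting the baseline value fixes its weight at 1, whereas adjustment lets the data choose the weight.

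Two things are at stake. First, precision: the denominator of a ratio is where extra noise does most harm, particularly if the true gain in suppression is small. Second, consistency: within one trial the two estimators will usually give different numbers, so the effectiveness result and the cost-effectiveness result for one outcome could disagree. The ICER is then to be set against a WHO threshold and national health spending, so this number is the one decision-makers will use.

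**Working it through.** **Inputs from the protocol (Sample Size, Study Design).** 40 clinics allocated equally, 40 completers per clinic, so 800 per arm; ICC 0.05; over-time correlation 0.50, stated for self-reported adherence; baseline good adherence 65%; 84% power at two-sided 5%.

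**Assumptions.** The protocol gives no suppression rate, effect on suppression, ICC for suppression or correlation for suppression. I assume 70% against 75% at month 12, carry the ICC of 0.05 across, and vary r from 0.3 to 0.9.

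**Step 1: the protocol's own figure.** Design effect = 1 + (40 − 1) × 0.05 = 2.95. Effective number per arm = 800/2.95 = 271.2. With baseline adjustment the variance factor is 1 − r² = 1 − 0.25 = 0.75.

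For adherence of 65% against 75% (a 15.4% relative gain), the unpooled SE is √[(0.2275 + 0.1875) × 0.75/271.2] = 0.0339. Then z = 0.10/0.0339 − 1.96 = 0.99 and power is 83.9% (83.7% with pooled variance). This matches the stated 84%. With a change-score factor of 2(1 − r) = 1.00, pooled power is 72.1%.

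Other readings of the 15% improvement do not match:
- An exact 15% relative gain (65% to 74.75%) with adjustment gives 81.7% pooled and 82.0% unpooled.
- A 15-point gain (65% to 80%) gives 97.6% without and 99.5% with adjustment.

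So the adherence sizing is consistent with reliance on baseline adjustment. The article does not give its formula, so this is not proof.

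**Step 2: the two estimators compared.** Relative to comparing month-12 proportions alone, the variance factor is 2(1 − r) for a difference in changes and 1 − r² for baseline adjustment. Their ratio is 2(1 − r)/[(1 − r)(1 + r)] = 2/(1 + r), which exceeds 1 for every r below 1.

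**Step 3: size for suppression.** The unadjusted SE is √[(0.70 × 0.30 + 0.75 × 0.25)/271.2] = √(0.3975/271.2) = 0.0383. Multiplying by the square root of each factor gives:

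| r | Factor, change | Factor, adjusted | Variance ratio | SE ratio | 95% half-width, change (points) | 95% half-width, adjusted (points) |
|---|---|---|---|---|---|---|
| 0.3 | 1.40 | 0.91 | 1.54 | 1.24 | 8.9 | 7.2 |
| 0.5 | 1.00 | 0.75 | 1.33 | 1.155 | 7.5 | 6.5 |
| 0.7 | 0.60 | 0.51 | 1.18 | 1.085 | 5.8 | 5.4 |
| 0.9 | 0.20 | 0.19 | 1.05 | 1.03 | 3.4 | 3.3 |

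At r = 0.5 the SEs are 0.0383 and 0.0332. Around a 5-point gain the 95% intervals are −2.5 to +12.5 points (change) and −1.5 to +11.5 points (adjusted). The chance of a zero or negative denominator is Φ(−0.05/0.0383) = 9.6% against Φ(−0.05/0.0332) = 6.6%. At this r the change-based estimate is no more precise than ignoring baseline altogether.

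**Step 4: check with clustering.** I simulated 40 clinics of 40 participants, with about 70% suppressed and a true difference of about 5 points, varying the stability over time of clinics and of individuals separately. Both estimators averaged about 5 points. The SD of the difference in changes was 1.00 to 1.22 times that of individual-level baseline adjustment; the ratio of 1.00 arose where clinic levels were most stable (0.9). Within one simulated trial the two estimates differed with an SD of about 2 to 3 points.

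**The case against.** The strongest reply is that the text supports less than a reader might infer from it. Four stronger readings are tempting, and the document supports none of them.

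- *The denominator is crude.* The section says it is calculated from the changes. It does not say unadjusted, and model-based proportions are not ruled out.
- *Sampling error will be ignored.* The article names no interval, but it does not say there will be none. The message-price example is open-ended. A condensed article may leave interval methods to the full protocol or analysis plan, so silence here is not a defect.
- *Every other model adjusts for baseline.* That statement sits under Primary Analyses. Mediation Analyses says only "The analytic approach will be based on path analyses using regression analyses or structural equation modeling", and Table 1 gives retention no baseline value.
- *The ICER rests on a different effect.* Under randomisation both estimators target the same risk difference, and the simulation showed no bias in either.

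The reply also has force on size. The correlation of 0.50 belongs to adherence; at higher r the loss shrinks to a few per cent, and with very stable clinics it can vanish. Both intervals above cross zero, so changing the estimator would not by itself make the ICER secure. A null effect on suppression would still be visible in the planned GEE test. Finally, Primary Analyses names no link function: a logit model would yield an odds ratio, which cannot serve as an ICER denominator, so some further step is needed in any case.

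All of this stands, and it limits the point. It does not remove the mismatch: one section states an estimator for an outcome for which another section plans a generally more precise one, and nothing connects them.

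**Conclusion.** The point holds as one of precision and consistency, not of bias. The article specifies a difference in changes for the ICER denominator and does not link it to the baseline-adjusted, cluster-aware analysis of the same outcome. The expected cost is an SE about 15.5% larger if the adherence correlation of 0.50 also applies to suppression, and 24% to 3% larger over an assumed r of 0.3 to 0.9. Using r = 0.50 and ICC 0.05 for suppression is an assumption, as are the 70% and 75% rates behind the interval widths. With clustering the gain from adjustment may be smaller or absent. The benefit in precision is therefore modest and not assured; the benefit of resting both objectives on one estimate does not depend on r.

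**What to change.** In Cost Effectiveness Analysis, define the denominator as the baseline- and strata-adjusted risk difference in viral suppression at 12 months from the model described under Primary Analyses. State the scale: an identity link, or marginal standardisation to a risk difference if the link is logit. Effectiveness and cost-effectiveness then rest on one estimate.

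Secondarily, carry the facility-clustered uncertainty of that estimate into the ICER, for example by resampling facilities within arm and stratum and refitting the model each time. Report this alongside the tornado diagram, which can stay as it is for prices and other inputs.

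The cost is a little more analysis work. Viral load is already measured at baseline and month 12, so no new data are needed. The study was stopped before ethics approval and new funding is being sought, so the change can be made before any implementation.

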**Health Outcomes**						
	ART adherence	Self-report in given time period; self-report via visual analog scale; pharmacy refills	Clinical care data; pharmacy records	X	X	X
	Viral suppression	Undetectable plasma HIV viral load (<400 copies/ml)	Laboratory testing	X		X
	Retention in care	Client tracking outcomes: stopped treatment, known to be dead, or lost to follow-up	Clinical care data		X	X
	Condom use	Consistency of use and use at last sex with different partners (main, casual)	Clinical care data	X	X	X

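### The only ICER is cost per additional virally suppressed patient, yet it is to be read against three times GDP per person with no link from suppression to a unit of health

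*Protocol article*

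**What the plan says.** All of this is in the protocol article.

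- **Numerator** (Cost Effectiveness Analysis): "the numerator for the ICER will be calculated as the additional costs associated with implementing the LifeLine program beyond the standard of care".
- **Denominator** (same section): "The denominator for the ICER will be calculated from the change in proportion virally suppressed at 12-month follow-up in the LifeLine intervention group", set against the corresponding change under standard of care. Table 1 defines the outcome as "Undetectable plasma HIV viral load (<400 copies/ml") and schedules it at baseline and month 12 only. The effect is therefore a difference between arms in change over two time points.
- **Unit of effect** (Abstract, Methods): the ICER is described "with health effects expressed in terms of viral load suppression and costs of resources used for the intervention". No life-year, QALY or DALY appears anywhere in the article.
- **Benchmark** (Cost Effectiveness Analysis): the WHO threshold for cost-effectiveness is brought in, and "an ICER lower than three times gross domestic product per person will be considered in presenting results from cost-effectiveness analyses". No unit of health is attached to it.
- **Other elements** (same section): "Sensitivity analyses will be conducted to model cost-effectiveness under different parameters, such as lower text message costs", to be shown in a tornado diagram. Affordability is a further yardstick: "intervention costs and the ICER will be compared to country expenditures on health".

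**The concern.** An ICER carries the unit of its denominator. Here that unit is one additional patient below 400 copies/ml, with nothing in it about duration, survival or quality of life. A money ceiling on an ICER states how much one unit of some health measure is worth. The two can be compared only if the units are the same, or if a conversion joins them. The article fixes both sides of the comparison and supplies neither condition.

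What is at stake is the conclusion for the third study objective. The Justification for Study section says decision-makers need such data to allocate resources, and the Conclusions section promises recommendations that include cost-effectiveness. A report that follows the text as written could call LifeLine cost-effective, or not, on a comparison that carries no information about value per unit of health.

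**Working it through.** The article gives no cost, no GDP figure, no expected suppression rate and no expected ICER, so there is no stated figure to reproduce. The check is one of units, with assumed values to show how much it matters.

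**Inputs**

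- *G*: GDP per person. The ceiling is 3G (Cost Effectiveness Analysis).
- *c*: added cost of LifeLine per participant, in multiples of G. Assumed, 0.02G to 0.3G. The denominator is a proportion, so the cost is put on a per-participant scale.
- *d*: difference between arms in change in the proportion suppressed. Assumed, 0.05 to 0.15.
- *k*: units of a generic health measure gained per additional suppressed patient. Assumed, 0.1 to 5.

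**Formulas**

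- ICER as planned = c / d, in money per additional suppressed patient.
- ICER per generic health unit = c / (d × k).
- The two are equal only if k = 1, which the article neither states nor argues.
- The converted ICER meets the ceiling exactly when c / (d × k) = 3G, that is at k = c / (3G × d). Below that k it exceeds 3G; above it, it is under 3G.

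**Main illustration**, c = 0.1G and d = 0.05:

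- Planned ICER: 0.1G / 0.05 = 2G, below 3G.
- k = 0.1: 2G / 0.1 = 20G, above.
- k = 0.5: 2G / 0.5 = 4G, above.
- k = 1: 2G, below.
- k = 5: 2G / 5 = 0.4G, below.
- Switch point: 2 / 3 = 0.67.

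**Across the assumed ranges**

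| c | d | c/d | k = 0.1 | k = 0.5 | k = 1 | k = 5 | switch k |
|---|---|---|---|---|---|---|---|
| 0.02G | 0.15 | 0.13G | 1.33G | 0.27G | 0.13G | 0.03G | 0.044 |
| 0.1G | 0.05 | 2G | 20G | 4G | 2G | 0.4G | 0.67 |
| 0.3G | 0.05 | 6G | 60G | 12G | 6G | 1.2G | 2.0 |

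The second row shows a planned ICER under the ceiling that goes over it after conversion when k is small. The third shows a planned ICER over the ceiling that comes under it at k = 5. The first shows a programme cheap enough to stay under the ceiling at every k in the table. So the comparison can mislead in either direction, or happen to be right, and without k nobody can tell which.

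**The case against.** **The threshold is only considered, not applied as a rule.** This stands. A reader might infer that three times GDP is a pass/fail criterion for objective 3. The text says only that it will be considered when results are presented, and it adds affordability as a second yardstick. But the article calls it a threshold for cost-effectiveness and states the cut-off, so a reader of the results will naturally take an above-or-below answer from it.

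**The unit of the WHO threshold lies in a source that is not at hand.** This also stands, and nothing here rests on what that source says. Whatever the ceiling's unit is, the article does not show that one suppressed patient is that unit.

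**The outcome is fixed in advance.** A reader might infer that the analysts could move the answer by choosing another outcome, such as adherence. The documents do not support this: viral suppression is the sole denominator, and no adherence-based ICER is planned.

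**The error need not flatter LifeLine.** A reader might infer that conversion always makes the ICER worse. That would follow only from assuming that each suppressed patient is worth less than one health unit, and the article gives no basis for that assumption.

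**A full costing plan might hold the conversion.** This is possible, since the article is condensed and its sensitivity analyses are open-ended. But the article is not silent on the matter. It specifies the denominator as suppression and then cites a cut-off for an ICER, having defined only that one. The one sensitivity parameter it names, message cost, belongs to the numerator.

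**Conclusion.** The concern holds as a mismatch of units within the Cost Effectiveness Analysis section. Cost per additional suppressed patient is a valid ICER as defined. Setting it beside three times GDP per person is what cannot support a statement about cost-effectiveness.

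No single size can be given. Over the assumed costs and effects, the planned ICER runs from 0.13G to 6G, and the health value per suppressed patient at which the comparison changes sides runs from 0.044 to 2.0 units. All values of c, d and k are assumptions; the mismatch itself needs none of them.

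The point affects how objective 3 is interpreted. It does not affect the randomisation, the sample size, the data collection or the comparison of health outcomes between arms. It is worth correcting because the trial has not started and the article offers its methods as guidance to others.

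**What to change.** Do not apply the GDP threshold to the suppression-based ICER. Report cost per additional suppressed patient with its uncertainty, together with the affordability comparison already planned.

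If the threshold is to be kept:

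1. State the unit of health to which it refers.
2. Convert additional suppressed patients to DALYs or QALYs with a stated conversion and time horizon.
3. Vary that conversion over a stated range in the planned tornado diagram, beside message cost.
4. Apply the threshold only to the converted ICER.

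The first option costs the loss of a simple benchmark and the edit of one sentence. The second costs a small modelling step that needs outside inputs. Neither needs new data from participants.
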